### The intervention: NIGRAAN training package

The NIGRAAN intervention applies at the cluster level. Each of the LHSs, the primary targets of the intervention, constitutes a cluster. Through the LHSs, the intervention targets LHWs at the cluster level too.

The intervention consists of the following components:

#### A. Training

In a 4-day training workshop, a training consultant would facilitate the 17 LHSs in the intervention arm to improve their theoretical and practical understanding of management of childhood diarrhoea and pneumonia and clinical mentoring and supervision skills. Special focus would be to improve LHS skills in providing verbal and written feedback to their assigned LHWs. The face-to-face learning would be complemented by hands-on training in the hospital setting along with practical exercises in a simulated environment. The instructional methodologies used during the training would include interactive lectures complemented with audio-visual aids/videos (to be sourced through WHO) and role plays, etc. Prior to the NIGRAAN specific training (described above), a 2-day refresher training based on all aspects of existing LHW curriculum would be offered by master trainers (trained through the project) for all the 34 LHS in both arms.

#### B. Supervisory tools

To complement the existing LHW Management Information System, NIGRAAN intervention will also introduce the following tools:The ‘Modified Supervisory Checklist’ has been adapted from the existing LHW-P Management Information System kit for LHSs. It augments certain components to strengthen the monitoring of community case management of LHWs by LHSs and adds the feature of direct observation.The ‘Supervisor’s Tally Sheet for Compilation of Quality of Case (QoC) Management’ is the consolidated version of the modified supervisory checklist providing at a glance view of the progress and quality of case management as well as picks up the gaps in case management practices of LHWs working under a given LHS.The ‘LHS Feedback Card’ for individual LHWs is the most important tool in the intervention package. It aims to introduce the practice of written feedback to be provided to LHWs through LHSs.

Various components of NIGRAAN intervention package are shown in Figure 4.

**Figure 4 Fig4:**
[figure not shown]
**NIGRAAN intervention package.**

#### Potential harms and mitigation

We do not anticipate any risk to primary caregivers of children under 5. However, whilst NIGRAAN is feeding seamlessly into an already existing government system and is not deviating from existing LHW/LHS charter of duties, it is remotely possible that LHWs and LHS may experience higher levels of work-related stress and pressure. FGDs will be conducted regularly to assess the feasibility of continuing the intervention. If self-reported work pressure is noted and some LHSs feel overburdened and stressed out as a result of ‘a new way of doing the same things’ i.e. written instead of a verbal feedback and more stringent clinical mentoring of LHWs by LHS for the management of pneumonia and diarrhoea, stress-mitigating steps such as counselling and supportive consultation efforts will be taken in those clusters where such a stress is experienced. On-ground counselling will also be offered by the research team, to LHWs reporting increasing stress and difficulty in coping.

### Data collection instruments

Quantitative instruments have been developed to collect the appropriate population level data from the community as well as to measure the performance of the health workers—LHSs and LHWs—on the knowledge and skills domains. On the other hand, qualitative instruments will explore the structural gaps in the LHW-P and health workers’ basic knowledge and skills related to CCM of childhood diarrhoea and pneumonia.

#### Quantitative instruments

Skills assessment scorecard A: lists the variables for assessing clinical case management skills of LHWs and LHSs. Each item on the scorecard is linked with the essential tasks related to CCM of pneumonia and diarrhoea in children under 5.Skills assessment scorecard B: will be used for assessing supervisory and clinical mentorship skills of an LHS. This will incorporate elements of clinical mentoring and supportive feedback.‘Independent evaluators’ with relevant background and training in community health and clinical care will be recruited to accompany the health workers during her home visits and fill the scorecards.Household survey questionnaire: will be used for baseline and end-line household survey to collect data on caregiver knowledge and practices.Knowledge assessment questionnaire: will be used to assess LHS and LHW knowledge regarding CCM of pneumonia and diarrhoea in children under five. This instrument, in addition to being deployed pre intervention, will also be used periodically to assess change in LHS and LHW knowledge and skills.Table 1 provides an overview of the various quantitative tools.

**Table 1 Tab1:** **Overview of NIGRAAN quantitative tools**

**Tools/instruments**	**Purpose**	**User(s) in the field**
*Household survey questionnaire*	To record the socio-demographic information and caregiver practices regarding diarrhoea and pneumonia of the population under study as well as to document the morbidity due to diarrhoea and pneumonia	*The data collection team*
*Knowledge assessment questionnaire*	To assess the theoretical understanding and knowledge of LHSs and LHWs regarding community case management of diarrhoea and pneumonia	*The research team*
*Skills assessment scorecard ‘A’*	To assess the practical/clinical skills of LHSs and LHWs regarding community case management of diarrhoea and pneumonia	*Independent evaluator(s)*
*Skills assessment scorecard ‘B’*	To assess the supervisory and clinical mentoring skills of LHSs in terms of providing feedback and supportive supervision to LHWs	*Independent evaluator(s)*

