#### Blinding

After assignment to intervention and control clusters, all participants, field staff, independent evaluators (IEs), and data entry personnel will be blinded. For this purpose, control and intervention cluster LHSs and LHWs will be assigned study IDs with the key available only to the core Aga Khan University research team.

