**Table 2 Tab2:** **Relevance of NIGRAAN outcomes with the major assessments, relevant study instruments and timelines**

**Outcomes**	**Measurements**	**Timepoints**
*Primary outcome:*	Baseline, and end-line household surveys to assess change in community caregiver practices for management of childhood diarrhoea and pneumonia	*Baseline:* at 4–6 months
*Improvement in community case management (CCM) practices of diarrhoea and pneumonia*		*End-line:* at 20–22 months
*Secondary outcome 1:*	*Qualitative tools:*	*Qualitative tools*
*Improved perceptions, knowledge and skills among LHSs for community case management of pneumonia and diarrhoea in children under 5*	Focus group discussions (FGDs) and in-depth/key informant interviews	Once in each of the three phases of the project
	*Quantitative assessments:*	*Quantitative assessments*
	Knowledge assessment questionnaire and skills assessment scorecards ‘A’ and ‘B’	KAQs and scorecards: phases I and II on a periodic basis.
*Secondary outcome 2:*	*Qualitative tools*	*Qualitative tools*
*Improvement in LHWs perceptions, knowledge, skills and performance as a result of ‘structured supportive supervision’ by LHSs*	Focus group discussions (FGDs) and in-depth/key informant interviews	Once in each of the three phases of the project
	*Quantitative assessments:*	*Quantitative assessments*
	Knowledge assessment questionnaire and skills assessment Scorecards ‘A’ and ‘B’	KAQs and scorecards: phases I and II on a periodic basis.

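### Table 1 gives the knowledge questionnaire to the research team, which is not listed as blinded and whose core members hold the allocation key, so people who can know the arm may collect part of both secondary outcomes

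*Protocol article*

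**What the plan says.** The Blinding section states that after assignment "all participants, field staff, independent evaluators (IEs), and data entry personnel will be blinded". LHSs and LHWs carry study IDs, "with the key available only to the core Aga Khan University research team".

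Table 1 lists each quantitative tool with its purpose and its user in the field. The household survey questionnaire goes to the data collection team and both skills scorecards go to independent evaluators. The KAQ, whose purpose is "To assess the theoretical understanding and knowledge of LHSs and LHWs regarding community case management of diarrhoea and pneumonia", goes to "The research team".

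The section on quantitative instruments says that, besides its use before the intervention, the KAQ "will also be used periodically to assess change in LHS and LHW knowledge and skills". Table 2 makes it a quantitative measure for secondary outcome 1 (LHSs) and secondary outcome 2 (LHWs), with the timing "KAQs and scorecards: phases I and II on a periodic basis".

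**The concern.** Three of the four tools are in the hands of people who are either named as blinded or are distinct from the group with the key. The KAQ is the exception: its user is a team that is missing from the blinded list and that includes the key holders.

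The plan of data analysis compares changes before and after the intervention between arms. If the person giving or marking the KAQ knows the arm, and that knowledge affects help given during completion or leniency in marking, the effect enters the between-arm contrast directly and would look like a gain in knowledge. At stake is the credibility of the quantitative knowledge component of both secondary outcomes.

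**Working it through.** The point rests on who does what, so the main check sets the statements side by side. The plan gives no figure on this point to reproduce.

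1. **Who is blinded.** Participants, field staff, independent evaluators and data entry personnel (Blinding). The research team is not named.
2. **Who holds the key.** Only the core members of the university research team (Blinding).
3. **Who uses each tool.** Table 1 separates three groups: data collection team, independent evaluators, research team. Only the KAQ goes to the third. By contrast, independent evaluators "will be recruited to accompany the health workers during her home visits and fill the scorecards", and they are on the blinded list.
4. **Whether the KAQ is used after allocation.** Yes. Phase II is the intervention phase, and Table 2 places KAQs in phases I and II.
5. **Whether the KAQ counts as an outcome measure.** Yes, for both secondary outcomes in Table 2.
6. **Whether anything keeps KAQ users from the key.** No statement in the article does so.

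Items 2, 3 and 6 show that the same people could hold the key and use the KAQ. They do not show that the same people will.

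**Illustration of sensitivity.** Inputs from the protocol: 17 LHSs and 85 LHWs per arm, 5 LHWs per cluster, and an intra-cluster correlation of 0.122 (Sample estimates). The protocol does not tie that correlation to KAQ scores, so using it here is an assumption. The assessor shift b, in SD units, is also assumed: 0.1, 0.2 and 0.3.

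- LHWs: design effect = 1 + (5 − 1) × 0.122 = 1.488. Effective number per arm = 85 / 1.488 = 57.1. SE = √(2 / 57.1) = 0.187 SD.
- LHSs, one per cluster: SE = √(2 / 17) = 0.343 SD.
- With no true effect, the chance of a significant result is P(|Z + b/SE| > 1.96).

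| Assumed shift b | LHWs | LHSs |
|---|---|---|
| 0.1 SD | 8.3% | 6.0% |
| 0.2 SD | 18.8% | 9.0% |
| 0.3 SD | 36.1% | 14.1% |

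A smaller intra-cluster correlation would raise the LHW figures and a larger one would lower them. The normal reference is approximate with 34 clusters.

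**The case against.** The best answer is that the two passages may not describe the same people. The key goes to the core team, while Table 1 names the research team without that word, so the key holders may be a subset. Table 1 also speaks of users in the field, and field staff are said to be blinded, so a team member giving the KAQ in the field might count as blinded. A reader might infer that KAQ assessors do know the arm; the article does not establish that. What stands against the objection is that the article never says KAQ users are kept from the key, and Table 1 treats the research team as separate from the groups that are clearly protected. The section on potential harms also has the research team offering on-site counselling to LHWs under stress, with the new feedback and mentoring as the anticipated cause, so team members could learn the arm without the key.

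A reader might also infer that this team delivers the intervention, or is the only unblinded group. Neither is supported. A training consultant runs the intervention workshop and the LHSs carry the intervention forward. The consultant, who trains the 17 intervention LHSs, is not on the blinded list either.

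Finally, the mechanism is unproven. The article does not say whether the KAQ is self-completed, how items are formatted or who marks it. An article may leave such detail to the full protocol, so its absence is no fault. A self-completed form with fixed answers would leave little room for assessor influence. The assumed shifts are not evidence that bias of that size would occur, since any assumed bias inflates type I error. These limits bear on the size of the problem; the assignment in Table 1 still needs changing.

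**Conclusion.** The concern holds in a limited form. Followed as written, the plan allows people who can know the allocation to administer or mark a quantitative measure used after allocation for both secondary outcomes. Whether that will happen is not stated, and the Blinding section and Table 1 need to be reconciled.

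The scope is narrow. The primary outcome comes from the household survey, used by the data collection team. The scorecards, the other quantitative measures of the secondary outcomes, are filled by independent evaluators who are said to be blinded. Neither is affected.

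The size of any bias is unknown. The illustrative figures rest on assumed shifts and a borrowed intra-cluster correlation. They show only that a modest systematic difference in assessment would matter at these sample sizes, more for LHWs than for LHSs. The point is worth correcting because the remedy is simple and uses roles that the plan already has.

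**What to change.** - In Table 1, change the KAQ user from the research team to the independent evaluators or the data collection team, neither of which has access to the key.
- Have the forms marked against a preset answer key by staff who see only the study ID.
- In the Blinding section, state that anyone with access to the key neither administers nor scores any outcome instrument.

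The cost is brief training on the KAQ for the staff who take it over. According to the Trial status section, surveillance and the intervention had yet to start, so KAQs during the intervention phase could still be covered. Protection would be partial: only the intervention LHSs attend the 4-day workshop and issue feedback cards, so evaluators who accompany health workers may infer the arm. The change removes access through the key and does not guarantee full masking.

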#### Qualitative instruments

In-depth interview questionnaire:This semi-structured questionnaire will be used to guide the interviews with key informants in all phases of project NIGRAAN. This questionnaire uses open-ended questions to explore stakeholder knowledge about childhood pneumonia and diarrhoea, perspectives and experiences of health workers regarding supportive supervision and their experience and perceptions about the utility of NIGRAAN intervention.Focus group discussion guide:This tool will be used by FGD moderators to guide discussions. It consists of key probes and triggers to guide the discussion.

Table 2 provides an overview of major NIGRAAN assessments and activities, the relevant study instruments, and the timelines. The table also correlates the intended outcomes of the study with these assessments and time points of measurement.

**Table 2 Tab2:** **Relevance of NIGRAAN outcomes with the major assessments, relevant study instruments and timelines**

**Outcomes**	**Measurements**	**Timepoints**
*Primary outcome:*	Baseline, and end-line household surveys to assess change in community caregiver practices for management of childhood diarrhoea and pneumonia	*Baseline:* at 4–6 months
*Improvement in community case management (CCM) practices of diarrhoea and pneumonia*		*End-line:* at 20–22 months
*Secondary outcome 1:*	*Qualitative tools:*	*Qualitative tools*
*Improved perceptions, knowledge and skills among LHSs for community case management of pneumonia and diarrhoea in children under 5*	Focus group discussions (FGDs) and in-depth/key informant interviews	Once in each of the three phases of the project
	*Quantitative assessments:*	*Quantitative assessments*
	Knowledge assessment questionnaire and skills assessment scorecards ‘A’ and ‘B’	KAQs and scorecards: phases I and II on a periodic basis.
*Secondary outcome 2:*	*Qualitative tools*	*Qualitative tools*
*Improvement in LHWs perceptions, knowledge, skills and performance as a result of ‘structured supportive supervision’ by LHSs*	Focus group discussions (FGDs) and in-depth/key informant interviews	Once in each of the three phases of the project
	*Quantitative assessments:*	*Quantitative assessments*
	Knowledge assessment questionnaire and skills assessment Scorecards ‘A’ and ‘B’	KAQs and scorecards: phases I and II on a periodic basis.

### Plan of data analysis

All quantitative data would be primarily analysed in IBM SPSS version 19. Changes in community and health worker knowledge and case management practices of diarrhoea and pneumonia pre and post intervention will be compared between the intervention and control arms. Tests of significance will be performed.

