### Primary outcome

The primary outcome is improvement in CCM practices of childhood diarrhoea and pneumonia.

This outcome pertains to the cluster level as the intervention targets LHSs and through them their respective LHWs. It will be achieved through the following effects of the NIGRAAN intervention:Improved knowledge, skills and supervisory processes among LHSs for CCM of pneumonia and diarrhoea in children under 5Improvement in LHW knowledge, skills and performance as a result of structured supportive supervision by LHSsImproved knowledge of community caregivers through interactions with LHWs and LHSs during community management of children with diarrhoea and pneumonia

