#### Sample estimates

It was estimated that to achieve 80% power for estimating the effect of the intervention at 95% confidence interval and intra-cluster correlation coefficient of 0.122, 17 LHSs (1 LHS = 1 cluster) will be required for intervention and non-intervention arms each.

Five (5) LHWs will be selected in each cluster (85 each in intervention and control arm). These 170 LHWs are required to be able to detect the required number of diarrhoea and pneumonia cases in their catchment households for continuous skill assessment of LHWs and LHSs and to execute the intervention.

The sample for qualitative FGDs was drawn from the above pool of 170 LHWs at random with a target of 8–10 participants in each FGD.

To attain 80% power with 95% confidence interval for the baseline household survey, we estimated that at least 8,500 households will have to be selected in each arm (one LHW covers approximately 100 households). With a systematic randomisation of taking every fourth (4th) household with an expected number of one child under 5 years per household, at least 2,125 households will have to be approached in the baseline/endline survey in each arm to assess community caregiver practices for management of childhood diarrhoea and pneumonia. NIGRAAN baseline survey sampling strategy is depicted in Figure 3.

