**Overview of NIGRAAN sampling strategy for baseline survey.**

#### Allocation to intervention

LHSs were allocated to clusters based on a parallel design with 1:1 ratio. The allocation of 34 LHSs to intervention/control arm clusters was blinded at the cluster level and carried out through computer-generated randomised tables in computer software MS Excel. The process was carried out by a person not otherwise involved in the study.

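### If the planned comparison of pre-post changes is run on change scores, it is less efficient than end-line adjusted for baseline, and loses power against end-line alone when the cluster-level correlation is below 0.5

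*Protocol article*

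**What the plan says.** Under Plan of data analysis, the protocol article states: "Changes in community and health worker knowledge and case management practices of diarrhoea and pneumonia pre and post intervention will be compared" between the two arms, followed by "Tests of significance will be performed". It names no estimator, model or test. Table 2 gives the measurement of the primary outcome as "Baseline, and end-line household surveys to assess change in community caregiver practices for management of childhood diarrhoea and pneumonia", with baseline at 4–6 months and end-line at 20–22 months. The Primary outcome section adds: "This outcome pertains to the cluster level as the intervention targets LHSs and through them their respective LHWs".

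Sample estimates gives the design as "to achieve 80% power for estimating the effect of the intervention at 95% confidence interval and intra-cluster correlation coefficient of 0.122", for which "17 LHSs (1 LHS = 1 cluster) will be required for intervention and non-intervention arms each". It plans 2,125 households per arm at each survey. It gives no target effect, no outcome rate and no correlation between the two surveys. It also does not say whether the 80% is for an end-line difference or a difference in change.

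**The concern.** The most natural reading of the analysis sentence is that each cluster's baseline value is subtracted from its end-line value and the differences are compared. Subtraction forces a slope of 1 on the baseline. When the two surveys are only loosely correlated, it adds baseline noise to the outcome. With 34 clusters and surveys 14 to 18 months apart (20 − 6 and 22 − 4), that is possible. Adjusting end-line for baseline estimates the slope instead, so it uses the baseline only as far as it predicts end-line.

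Precision is at stake, not bias. Under randomisation both analyses estimate the same effect. The Abstract describes simple randomisation, so some chance baseline imbalance between arms should be expected. Both methods respond to it, but a change score over-corrects when r is low.

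**Working it through.** **Inputs from the article.** 17 clusters per arm (34 in all); 80% power; 95% confidence, read as two-sided alpha 0.05; ICC 0.122; 2,125/17 = 125 households per cluster per survey; about one child under 5 per household; pneumonia incidence 0.41 episodes per child-year.

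**Assumptions.** r, the cluster-level baseline/end-line correlation; equal variances at the two surveys; 80% power anchored on an unadjusted end-line comparison.

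**The plan's own figure.** The 17 clusters per arm cannot be reproduced, because no effect size is stated. The 80% is therefore taken as the starting point and not checked.

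**Efficiency.** Relative to end-line alone, the variance of the arm effect is 2(1−r) for a change score and 1−r² for baseline adjustment. The ratio is 2(1−r)/[(1−r)(1+r)] = 2/(1+r), which exceeds 1 for every r below 1.

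**Power.** The non-centrality that gives 80% on 32 df is 2.889. Divide it by the square root of the variance factor. Use 32 df for change and 34 − 3 = 31 df for adjustment.

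| r | 2(1−r) | 1−r² | 2/(1+r) | Change | Adjusted |
|---|---|---|---|---|---|
| 0 | 2.00 | 1.00 | 2.00 | 51% | 80% |
| 0.2 | 1.60 | 0.96 | 1.67 | 60% | 82% |
| 0.3 | 1.40 | 0.91 | 1.54 | 66% | 84% |
| 0.4 | 1.20 | 0.84 | 1.43 | 73% | 86% |
| 0.5 | 1.00 | 0.75 | 1.33 | 80% | 90% |
| 0.7 | 0.60 | 0.51 | 1.18 | 95% | 98% |

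The adjusted column leaves out the small cost of estimating the slope. A simulation with 17 clusters per arm, which includes it, gives 79%, 80%, 82%, 85%, 89% and 97% for the same rows. The change column does not move.

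**What r could be.** For independent samples of m respondents per cluster at each survey, r = CAC × m × 0.122/[1 + (m−1) × 0.122]. CAC is the cluster autocorrelation, an assumption. The article does not say whether the same households are revisited; if they are, r would tend to be higher.

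- *Items asked of every household, m = 125.* r = CAC × 15.25/16.128 = 0.946 × CAC, so r < 0.5 needs CAC below 0.5/0.946 = 0.53. Change against adjusted power is 98% v 99% at CAC 0.8, 85% v 93% at 0.6, 78% v 89% at 0.5 and 71% v 86% at 0.4.
- *Items limited to recent pneumonia.* m = 125 × 0.41 × weeks/52. The recall window is an assumption. At CAC 1:
  - 2 weeks: m = 2.0, r = 0.22, power 61% v 82%
  - 4 weeks: m = 3.9, r = 0.35, power 69% v 85%
  - 6 weeks: m = 5.9, r = 0.45, power 76% v 88%
  - 8 weeks: m = 7.9, r = 0.52, power 82% v 91%

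A CAC below 1 lowers r further.

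**The case against.** The strongest reply is that the article does not commit to raw change scores. Comparing change between arms is ordinary wording. With baseline as a covariate, the arm coefficient is the same whether the outcome is end-line or change. The analysis section is three sentences in a condensed article, and a fuller plan may specify adjustment. This stands to the extent that the point must be conditional on how the sentence is carried out. It does not remove the point, because both places that describe the comparison speak of change and neither mentions adjustment.

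A reader might infer that the trial is underpowered, well below its stated 80%. The article does not support that. The inference needs the 80% to refer to end-line and r to be below 0.5, and neither is stated. If the 80% was computed for change, there is no shortfall, and adjustment would raise power to about 95%, 90% and 84% at r = 0.2, 0.5 and 0.8. For items asked of all households, the article's own survey size and ICC point to a higher r unless cluster practices shift greatly between surveys. For the same reason, one cannot say that the sample-size calculation failed to allow for change scores.

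A reader might also infer that one baseline-adjusted end-line model suits every outcome at no cost. It does not. Table 2 has the knowledge questionnaires and scorecards repeated periodically. Their sampling depends on case surveillance that Trial status reports as still being set up, so those baselines cannot be assumed to be in hand.

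Finally, the result that adjustment never has larger variance is asymptotic. With 34 clusters a change score can be marginally better when r is close to 1, but the difference is small.

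**Conclusion.** The point holds as a matter of efficiency. If the planned comparison is run on change scores, its variance is about 2/(1+r) times that of end-line adjusted for baseline: 1.67 times at r = 0.2 and 1.33 times at r = 0.5. This assumes equal variances at the two surveys.

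The consequence for power is conditional. Power falls below 80% only if the 80% was set for end-line and r is under 0.5. That is plausible for case-management outcomes restricted to children with a recent episode, where only a few children per cluster contribute. It is unlikely for items answered by all 125 households in a cluster. This is a worthwhile and nearly free improvement to the stated analysis. It does not show that the design fails.

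**What to change.** For the primary household-survey outcome, replace the comparison of changes with a cluster-level regression of the end-line summary on arm and the same cluster's baseline summary, testing the arm effect with t on 31 df. An equivalent mixed model with the cluster's baseline value as covariate would also serve. Report pre-post change by arm descriptively.

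For the knowledge questionnaires and scorecards, model the repeated follow-up measures with adjustment for the pre-intervention value where one is obtained.

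The cost is a sentence or two of analysis wording and one degree of freedom, with power of about 79% instead of 80% if r is near zero. The baseline household survey has been done and the end-line survey is still to come, so the change can be fixed before end-line data are seen.
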